### Study population

Patients 65 years of age and older who are admitted to the medical ED will be identified by the ED staff as potential eligible patients. Subsequently, the ED staff will inform the research nurse. The research nurse will complete the eligibility criteria checklist (table 1). The research nurse will ask the patient and their informal caregiver (ie, partner, child, relative, friend) for their willingness to participate in the study and to provide written informed consent. The patient and informal caregiver will need to both sign the informed consent form before the patient can participate in the H@H trial.

**Table 1 T1:** Patient eligibility criteria for participation in Hospital at Home trial

Inclusion criteria	Exclusion criteria
Age 65 years of age and older Cognitive impairment, that is, dementia, delirium or other cause of cognitive impairment, and either Previously diagnosed or documented in the medical records or Identified by the ED clinician (eg, with the 4AT test and/or six-item cognitive impairment test)^42–44^ Presented at the ED with a defined acute illness Required hospital admission, according to the attending ED physician but not expected to require emergency interventions, Modified Early Warning Score ≤2 points^45–47^ Living in hospital’s catchment area (<25 km) Informal caregiver is present and able to understand and perform instructions and consented to participate in the trial Home suitable for Hospital at Home care (available informal caregiver, running water, adequate heating, safety)^44^	Previously enrolled Hospitalised within the 7 days preceding ED presentation Nursing home residents or awaiting a nursing home place on an active waiting list (excluding so-called sleeping waiting list candidates)^27^ Additional care needed: Required surgical assessment Suspected acute coronary syndrome or cardiac arrythmia^45^ Dialysis dependent patients^45^ Expected terminal events^45^ or in need of diagnostic or palliative care due to oncological or haematological illness

ED, emergency department.

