An evaluation to assess the mental capacity is conducted by the involved ED staff in the setting of the ED assessment. If the participant lacks the capacity to consent (mentally incapacitated), and an informal caregiver (ie, partner, child, friend) is present, this informal caregiver will be asked to act as a personal consultee. The personal consultee will determine whether he or she believes that participation in the study would be in accordance with the values and interests of the individual and will subsequently sign the patient’s informed consent form.

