### Study procedures

After (written) informed consent is obtained, all participants will complete two brief tests to assess cognitive impairment, and the participant and caregiver will complete the baseline assessment. Subsequently, randomisation takes place to either (1) the Hospital at Home care-intervention, translocation of care from the hospital to a participants’ home or (2) the control group, usual hospital care. All care will be delivered according to hospital protocols, current regulations and guidelines and, if needed, described in the standard operating procedures (SOPs). If no informed consent is given by either the patient or the caregiver, the reasons for non-participation, date of birth, sex of the patient and the relationship between patient and caregiver will be reported.

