#### Feasibility

For the participation rates, the proportion of participants per step will be calculated. The reasons for non-participation and data concerning the characteristics of non-participants will be collected. We consider the participation rate feasible when it is similar to the participation rate as is described in previous RCTs and around 50% of the eligible patients will consent to participate.^28 29^ Quality of care will be measured by collecting data on patient, institutionalisation (eg, to the hospital or nursing home), mortality, activities of daily living functioning, prevalence of hospitalisation-associated geriatric syndromes, the length of stay in the hospital or Hospital at Home care programme and contact with healthcare professionals. The study is considered feasible if the quality of care of Hospital at Home care on these measurements is non-inferior to usual hospital care.

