### Process evaluation

A process evaluation will be conducted as part of the feasibility study to understand the barriers and facilitators to participate and to gain an understanding of the experiences and perceptions of Hospital at Home care of participants and healthcare professionals. From all eligible patients who declined to participate, data concerning the patient characteristics and reasons for non-participation will be collected. At the end of the trial, a representative sample of participants and/or their informal caregivers will be invited for an interview to evaluate their experiences receiving Hospital at Home care. The interviewer will not be a an active member of the research team or involved in day-to-day care and will explore independently how the participants perceived Hospital at Home care, including the contact with the health professionals and the impact of Hospital at Home care on their lives and their caregivers’ personal lives. In case of participant dropout, efforts will be made to obtain an understanding of why the participants did not complete the trial.

In addition, a representative sample of healthcare professionals, consisting of physicians and nurses working in the ED, physicians and nurses providing the Hospital at Home care, and general practitioners, will be asked to participate in a face-to-face interview. The healthcare professionals will be asked about their experiences and opinions about the H@H trial and Hospital at Home care. All interviews will be transcribed verbatim, and a framework analysis will be used as the method of qualitative data analysis.^34^

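### Caregiver consent is listed as an inclusion criterion, which contradicts the rest of the article on who is eligible and can bias the participation rate upward

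*Protocol article*

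**What the plan says.** **Eligibility.** The inclusion column of Table 1 (Study population) requires "Informal caregiver is present and able to understand and perform instructions and consented to participate in the trial". The research nurse completes Table 1 as a checklist.

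**Consent.** The same section then describes asking patient and caregiver to take part, and states: "The patient and informal caregiver will need to both sign the informed consent form before the patient can participate in the H@H trial". Where the patient lacks capacity and an informal caregiver is present, "this informal caregiver will be asked to act as a personal consultee". The consultee judges whether taking part fits the patient's values and interests, and signs the patient's form.

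**Planning figures.** The sample size section takes 1900 patients per year in working hours. It finds about 15% eligible from ED medical records (285) and then applies a 50% consent rate to reach 143 inclusions. The 50% leans on two earlier trials, in which 54% and 57% of eligible patients consented.

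**Refusals.** Study procedures begins its rule on non-participants with "If no informed consent is given by either the patient or the caregiver, the reasons for non-participation" and adds a few descriptive items to be reported. Process evaluation says: "From all eligible patients who declined to participate, data concerning the patient characteristics and reasons for non-participation will be collected".

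**Criterion.** The Feasibility section states: "For the participation rates, the proportion of participants per step will be calculated". Participation counts as feasible when it resembles the earlier trials and "around 50% of the eligible patients will consent to participate".

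**The concern.** The participation rate belongs to the first listed objective, and recruitment is part of the primary aim. It is also the only feasibility criterion in the article with a number attached, since the other one, non-inferior quality of care, is given without a margin.

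A rate of consenting patients among eligible patients is informative only if eligibility is settled before consent is sought. Table 1 puts one of the required consents inside eligibility. Followed to the letter, a caregiver's refusal makes the patient ineligible, so a type of refusal that the rate should count disappears from it. Other sections count the same refusal as non-participation by an eligible patient.

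Two analysts could therefore work from the same screening log and report different rates, each with support in the text. If that choice is made after the counts are known, the target of about 50% loses much of its value as a prespecified benchmark, and a future trial could be planned on too high a recruitment yield.

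**Working it through.** **1. The plan's own figures.**
- Eligible per year: 1900 × 0.15 = 285.
- Expected inclusions: 285 × 0.50 = 142.5, rounded up to 143.
- Implied participation rate: 143/285 = 0.5018, or 50.2%.

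Both stated figures reproduce. Consent is applied after the 285 has been formed, and the 285 comes from medical records, which would not normally show whether a caregiver agreed to this trial. The planning denominator is thus a pre-consent one.

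**2. The sections side by side.**

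| Section | Status of a patient whose caregiver refuses |
|---|---|
| Study population, Table 1 | Fails an inclusion criterion, so not eligible |
| Study population, text | Checklist is described first, consent from both parties after it |
| Sample size | Eligible; consent applied afterwards |
| Study procedures | Non-participant, with reasons reported |
| Process evaluation | Decliners are described as eligible |
| Feasibility | Rate is among eligible patients, reported per step; the text does not list the steps |

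No section says which of the two statuses governs the participation rate.

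**3. Effect of the literal Table 1 reading.** The article gives no share of caregiver refusals, so I assume 5%, 10% and 20% of 285. With r caregiver refusals removed and 143 patients enrolled, the displayed rate is 143/(285 − r).

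| Assumed share | r | Denominator | Displayed rate | Shift from 0.5018 |
|---|---|---|---|---|
| 0% | 0 | 285 | 0.5018 | none |
| 5% | 14 | 271 | 0.5277 | 2.6 points |
| 10% | 28 (28.5 rounded down) | 257 | 0.5564 | 5.5 points |
| 20% | 57 | 228 | 0.6272 | 12.5 points |

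Of the 285 − 143 = 142 non-participants, these caregiver refusals make up 14/142 = 10%, 28/142 = 20% and 57/142 = 40%.

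**4. The reverse question.** If a share c is removed and the displayed rate is 50%, the rate among all patients meeting the non-consent criteria is 0.50 × (1 − c): 47.5% at 5%, 45.0% at 10% and 40.0% at 20%.

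**5. Scale.** The 95% sampling half-width at 50% with 285 patients is 1.96 × √(0.25/285) = 0.058, or 5.8 points. The shifts at assumed shares of 5% and 10% lie within it; the shift at 20% is about twice as large. Unlike sampling error, the shift always goes upward.

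**The case against.** The strongest reply is that Table 1 is only loosely drafted and the intended procedure is clear elsewhere. Consent is sought after the checklist, caregiver refusal is recorded as non-participation, decliners are called eligible, proportions are reported per step, and a CONSORT flow diagram will show declination rates. The trial flow chart is not available here and may define the steps, and a condensed article need not carry every denominator. Much of this stands. The article never states removal from the denominator as a counting rule, and because refusals are recorded, the rate can be recalculated with them included. It does not dispose of the point, which is not a missing definition: a stated criterion conflicts with other stated text.

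Three stronger readings are tempting and not supported.

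- **That the rate will be inflated.** This follows only if Table 1 is applied literally, and most of the other text points away from that.
- **That participation among patients without capacity would approach 100% by construction.** Table 1 concerns the caregiver's own consent. The consultee's judgement about the patient's values and interests is a separate act. A caregiver could accept their own role and still judge that the patient would not want to take part, and that refusal would stay in the denominator even under Table 1.
- **That a failed target would be turned into a pass.** This needs an assumed refusal share, and a criterion worded as around 50% and similar to earlier rates is not a sharp line.

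**Conclusion.** The point holds as a contradiction with a possible upward bias. Table 1 makes caregiver consent part of eligibility, while the sample size section, Study procedures and Process evaluation treat eligibility as settled before consent. The denominator of the only numerical feasibility criterion therefore has two defensible readings.

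The direction of the bias under the literal reading is certain for any non-zero number of caregiver refusals. Its size cannot be derived from the article. Under the assumed shares of 5% to 20%, with 285 patients meeting the other criteria and 143 enrolled, 50.2% would read between 52.8% and 62.7%. Nothing here touches randomisation or the comparison between arms.

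**What to change.** 1. In Table 1, keep the requirement that a caregiver is present and capable of carrying out instructions. Take the caregiver's consent out of the criteria and place it in the consent step described in Study population and Study procedures.
2. In the Feasibility section, define the participation rate as patients with all required consents divided by all patients who meet every non-consent criterion.
3. State that refusals by the patient, the caregiver or the consultee all remain in the denominator, and show the three counts separately.

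This costs one table row and one definition. Study procedures already provides for recording these refusals with reasons, so the rate needs no extra data; the breakdown needs only that the recorded reason shows who refused. The downside is that the reported rate may look less favourable than under the literal Table 1 reading.

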### Sample size of study population

Based on the numbers available from the ED of the University Medical Center Groningen, the Netherlands, we calculated that an average of 3990 older patients 65 years and over is admitted to our medical ED each year. The Hospital at Home trial will be introduced during working hours, which provides an estimated 1900 patients per year. Not all 1900 patients will be eligible for study inclusion. Based on screening of ED medical records, approximately 15% of the patients meet the eligibility criteria for Hospital at Home care, resulting in 285 eligible persons per year. In recent randomised controlled trials (RCTs) of Hospital at Home care in Italy, 54% and 57% of the eligible patients was willing to participate and gave informed consent.^28 29^ We presume a similar consent rate of 50%, as described in these previous clinical trials, and expect for 143 patients to be included.

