Whether Hospital at Home care provides a suitable alternative with regard to other outcomes as patient satisfaction, quality of care, hospitalisation-associated adverse events and costs in older people with cognitive impairment remains unclear and further research is needed. Therefore, our primary aim is to investigate the feasibility of a Hospital at Home care programme for older patients with cognitive impairment in terms of the patient recruitment, use and acceptability, and second to investigate the advantages and disadvantages of Hospital at Home care compared with usual hospital care from different perspectives.

Objectives of this study are the following:To assess the participation rate of the Hospital at Home trial among patients 65 years and older with cognitive impairment, acute illness and emergency hospital admission. What are the reasons for non-participation?To assess the potential advantages and disadvantages of Hospital at Home care and usual hospital care for the patients, caregivers and Dutch medical health system.To assess the feasibility of Hospital at Home care in terms of the quality of care with regard to geriatric syndromes, institutionalisation, mortality, total days with urinary catheter, length of stay (in the hospital or in Hospital at Home care) and timing/intensity of the contact with healthcare professionals.

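### The recruitment criterion tests only consent among eligible patients, so it can be met however few patients turn out to be eligible, and its denominator is not consistently defined

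*Protocol article*

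**What the plan says.** All references are to the protocol article.

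- **Background.** The main purpose of the study is given as: "feasibility of a Hospital at Home care programme for older patients with cognitive impairment in terms of the patient recruitment, use and acceptability".
- **Sample size of study population.** The planning chain starts from 3990 older patients a year and narrows to those seen when the trial is staffed: "The Hospital at Home trial will be introduced during working hours, which provides an estimated 1900 patients per year". Eligibility comes next: "Based on screening of ED medical records, approximately 15% of the patients meet the eligibility criteria for Hospital at Home care". The article puts this at 285 a year. Consent is a separate, later step: "We presume a similar consent rate of 50%, as described in these previous clinical trials, and expect for 143 patients to be included".
- **Feasibility.** The recruitment criterion reads: "We consider the participation rate feasible when it is similar to the participation rate as is described in previous RCTs". It adds that about half of those eligible should consent. Proportions for each step are to be calculated, but no threshold is set for the share eligible, the number eligible or the number enrolled. A separate condition requires that quality of care is non-inferior.
- **Study population, Table 1.** One inclusion criterion is: "Informal caregiver is present and able to understand and perform instructions and consented to participate in the trial".
- **Study procedures.** If either the patient or the caregiver withholds consent, the case is recorded as non-participation, with reasons.

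**The concern.** Enrolment is the product of three quantities: patients presenting, the fraction eligible and the fraction of those who consent. The plan gives a figure for each, but its criterion acts on the last alone. A study that found far fewer eligible patients than planned, with half of them consenting, would meet its own recruitment criterion while missing its expected enrolment by a wide margin. For a trial whose primary aim includes recruitment, that is a weak test.

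The denominator adds a second problem. If caregiver consent is part of being eligible, a refusing caregiver removes the patient from the denominator. If it is part of participating, the same refusal lowers the rate. The verdict could then turn on how refusals are classified.

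**Working it through.** **Inputs.** From the sample size section: 1900 presenting patients per year, yield 15%, consent 50%. From Trial design: allocation 4:1, so one fifth are controls.

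**The plan's own figures.**
- Eligible: 1900 × 0.15 = 285.
- Included: 285 × 0.50 = 142.5, given as 143.
- Enrolled over presenting: 143 / 1900 = 7.5%.

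The stated figures reproduce. The 143 is an annual number because it derives from 285 per year.

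**The criterion as a formula.** With N presenting, yield y and consent c, the statistic is consenters / eligibles = (N × y × c) / (N × y) = c. The yield cancels.

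**Varying the yield with consent held at 50%.** Only the 15% row comes from the article. The other yields are assumptions chosen to show the behaviour.

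| Yield | Eligible per year | Included per year | Controls (one fifth) | Consent among eligibles | Enrolled / presenting |
|---|---|---|---|---|---|
| 15% | 285 | 142.5 | 28.5 | 50% | 7.5% |
| 10% | 190 | 95 | 19 | 50% | 5.0% |
| 5% | 95 | 47.5 | 9.5 | 50% | 2.5% |

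The criterion is met in every row. At 5% the shortfall against plan is 1 − 47.5/142.5 = 67%. Enrolled over presenting, by contrast, falls in step with the yield.

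The yield affects the criterion only through precision. The 95% half-width around 50% is 1.96 × √(0.25/n), which is 5.8 percentage points with 285 eligible and 10.1 with 95. A smaller eligible pool therefore makes it harder to tell whether the rate really is around 50%.

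**The denominator.** Illustration with assumed counts: 100 patients meet every criterion apart from consent, 30 caregivers refuse, and 35 patients enrol.
- Caregiver refusal counted as non-participation (Study procedures): 35 / 100 = 35%.
- Caregiver refusal counted as ineligibility (Table 1): 35 / (100 − 30) = 35 / 70 = 50%.

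The same recruitment gives 35% under one reading and 50% under the other.

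**The case against.** The strongest reply is that a shortfall would not be hidden. Proportions per step will be calculated, and a CONSORT flow diagram will summarise recruitment, so anyone planning a later trial would see the observed numbers. This stands. It means that the harm is a criterion that passes when it should not, not a loss of information. A reader might infer that a future trial would be planned on 285 and 143 regardless of what was observed. The article does not say so.

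Second, the criterion speaks of the participation rate, and feasibility of the study has a separate quality-of-care condition. This also stands. A reader might infer that the whole study would be declared feasible on consent alone, but the text does not support that. The point concerns the recruitment verdict only.

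Third, a condensed article may leave further progression targets to the full protocol. That is possible. But the article does state a recruitment criterion, and as stated it does not respond to the yield.

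A stronger reading is tempting: that 15% is too high because past records cannot show caregiver consent, caregiver ability or home conditions, so that 143 is a ceiling. The document does not support it, for three reasons.
- Consent enters as its own 50% step after the 15%, so faulting the 15% for omitting consent would count it twice.
- The article does not say which fields were screened. That records lack caregiver and home information is plausible but unverified.
- The error could run the other way. Table 1 admits patients whose impairment is first identified in the emergency department, and past records may miss them. The assumed 50% consent is also below the 54% and 57% cited, which would give 285 × 0.54 = 154 and 285 × 0.57 = 162.

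**Conclusion.** The concern holds for the recruitment criterion. As written, it cannot respond to a shortfall in eligible patients: at 50% consent it is met with 143, 95 or about 48 included per year. That the criterion does not depend on the yield is exact and follows from its form. The yields of 10% and 5% are assumptions, and the article gives no basis for preferring either. Eligibility is also defined inconsistently with respect to caregiver consent, and the direction of that effect is known: counting refusing caregivers as ineligible raises the rate.

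The article does not show that 15% is wrong. The figure is uncertain in both directions, which is a reason to test it, not to lower it in advance.

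**What to change.** **Feasibility section.**
- Define an eligible patient as one who meets all Table 1 criteria before any consent by patient or caregiver. Count refusal by either as non-participation, in line with Study procedures.
- Judge recruitment on the consent proportion together with one further quantity. This can be the observed yield (eligible over presenting patients aged 65 and over in working hours, planned 15%) or enrolment (enrolled over presenting, planned 143/1900 = 7.5%, or the number enrolled per year).
- State in advance a minimum for that quantity, chosen by the sponsor. The planned values are the natural comparison but, being uncertain, need not be the pass mark.

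**Sample size section.** Say which Table 1 criteria the record screen applied, and mark 285 and 143 as uncertain in either direction. They should not be relabelled as upper estimates, and no lower bound should be written in without data behind it.

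**Cost.** The change is mostly wording, and the recruitment verdict becomes harder to meet. There is one practical demand. Emergency department staff identify potential patients before the research nurse applies the checklist, so the number presenting must be logged as the first step.
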